### Sample size

The expected effect size and attrition rates are based on former trials that studied the effects of cognitive-behavioral group interventions for children with CI. Generally, psychological interventions for children with CI indicated medium effect sizes (mean ES = 0.71, range = 0.28-3.23, SD = 0.61) [6]. In a study that evaluated cognitive-behavioral group interventions for children with anxiety disorders, enhanced by parental involvement also medium effect sizes were found [19]. Based on four repeated measurements with within-subject correlations of .5, a sample size of 126, 42 in each condition, is necessary to achieve adequate power (.80) to trace differences of medium effect size (d = .5) between the conditions over time at a significance level of .05 [20]. To be able to control for dependency effects (block and centre effects) and taking into account 10% attrition over time, 162 children have to be recruited to reach the required sample size.

### Outcomes measures

Participating children, and one of their parents, are asked to complete questionnaires at baseline, 6 weeks, 6 months and 12 months after baseline. Primary caregivers are asked to fill in questionnaires and to participate in the parent intervention. All questionnaires are assessed online; participants receive an email with a unique link to the questionnaires. Total duration time for filling in the questionnaires is estimated on 45 minutes for children and 35 minutes for the parents.

#### Questionnaires

For this study an adapted version (12 items) of the Coping Strategies Inventory (CSI) will be used [21]. All other outcome measures will be assessed by standardized questionnaires with good psychometric qualities, and available normative data [22-33] (Table 2).

**Table 2 T2:** Primary and secondary outcome measures, measurement instruments, and informant.

Primary outcome measures	Measurements	Informant
Psychosocial functioning	Child Behaviour Checklist (CBCL) [22]	parent
	Youth Self-Report (YSR) [23]	child (age11-18)
	Strengths and Difficulties Questionnaire/4-18 (SDQ parent and child report) [24,25]	parent & child (11-18)
Disease related coping skills	Questionnaire Op Koers for children (QOK-c, 18-items) [1]	child (8-18)
	Questionnaire Op Koers for parents (QOK-p, 18-items) [1]	parent
		
**Secondary outcome measures**	**Measurements**	**Informant**

Quality of life	KIDSCREEN-27 [26]	child (8-18)
	DISABKIDS Chronic Generic Measure - short form (DCGM-12) [27,28]	child (8-18)
General coping skills	Adapted version of the Coping Strategies Inventory (CSI) [21]	child (8-18)
Self perception	Self-perception Self-Perception Profile for Children (CBSK) [29]	child (8-12)
	Self-Perception Profile for Adolescents (CBSA) [30]	child (12-18)
Parental stress	Nijmegen Parenting Stress Index-Short (NPSIS) [31]	parent
Parent - child interaction	Family Interaction Task (FIT) is a 30-minute semi-structured observation¹ [34]	observation
	Security Scale [32]	child (8-18)
Perceived vulnerability	Dutch version of the Parental Vulnerability Scale (8 items) [33]	parent

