### Inclusion and exclusion criteria

For inclusion, children between 8 and 18 years old and suffering from a chronic illness are selected. The term 'chronic illness' refers to illnesses that require at least 6 months of continuous medical care, permanent life style changes and continuous behavioral adaptation to the unpredictable course of the illness [2]. Children who attend special education due to severe learning difficulties are excluded, because for these children an adapted or individual program might fit better to their individual cognitive needs. The final criterion is that children and parents should be able (with help) to fill in Dutch questionnaires.

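### The stated power of .80 does not apply to two of the six primary measures (YSR and SDQ child form), which only children aged 11-18 complete in a trial of ages 8-18

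*Protocol article*

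**What the plan says.** Under Inclusion and exclusion criteria, "children between 8 and 18 years old and suffering from a chronic illness are selected". The Interventions section describes a separate programme version for ages 8-12, and the Randomization section schedules the conditions separately for each age group. Younger children are therefore part of the design.

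Under Sample size, "a sample size of 126, 42 in each condition, is necessary to achieve adequate power (.80"; the target is "differences of medium effect size (d = .5) between the conditions over time", "at a significance level of .05", based on "four repeated measurements with within-subject correlations of .5". The recruitment target is 162, which covers 10% attrition and block and centre effects. No instrument or age subgroup is named.

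Table 2 (Questionnaires) lists these primary measures:

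| Outcome | Measure | Informant and age |
|---|---|---|
| Psychosocial functioning | CBCL | parent |
| | YSR | "child (age11-18" |
| | SDQ, parent form and child form | "parent & child (11-18" |
| Disease-related coping | QOK-c | child, 8-18 |
| | QOK-p | parent |

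Counting the two SDQ forms separately, there are six primary reports. The age limit of 11 applies to the YSR and the SDQ child form only.

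**The concern.** The two age-limited forms are the only child self-reports of psychosocial functioning, the first primary outcome named. Children aged 8 to 10 cannot contribute to them, yet the single sample size reads as if every child contributes to every primary measure. The article ranks no primary measure above another, and its Discussion calls the sample sufficient for comparing the intervention conditions with control.

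At stake is how a null result on the YSR or the SDQ child form would be read. A reader who trusts the Sample size section would take it as evidence from a test with 80% power, applying to ages 8-18. It would in fact come from a smaller group, with lower power, and say nothing about children under 11.

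**Working it through.** **Inputs from the Sample size section:** d = .5, significance level .05 (two-sided is assumed, as the article does not say), power .80, four measurements, within-subject correlation .5, 42 per condition, 162 recruited, 10% attrition.

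**Step 1: reproduce the plan's figure.** For two arms compared on the mean of the three post-baseline measurements, the variance factor is VF = (1 + 2 × .5)/3 = .667. The change from baseline to that mean has the same factor at a correlation of .5.

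n per arm = 2 × VF × (1.96 + .8416)² / d² = 2 × .667 × 7.849 / .25 = 41.86, rounded up to 42, or 126 in three arms. Power at 42 is .801. The stated figure reproduces.

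**Step 2: the allowance in 162.** 162 × .9 = 145.8, or 48.6 per arm. 145.8/126 = 1.157, so about 16% is left for block and centre effects. With the allowance needed in full, the effective number is 42 per arm; with no dependency at all, it is 48.6.

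**Step 3: share aged 11 or older.** The article gives no age distribution, so these are assumptions:
- Half of the children in each age group, evenly spread within 8-12: .5 × 1/4 + .5 = 62.5%.
- Even spread over 8 to 18: 7/10 = 70%.
- Eight of eleven year-ages (18 included): 8/11 = 73%.

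**Step 4: power for the YSR or SDQ child form.** Power = Φ(d / √(2 × VF / n) − 1.96). Example at 62.5%: n = 42 × .625 = 26.25; √(1.333/26.25) = .2254; .5/.2254 = 2.219; 2.219 − 1.96 = .259; Φ = .602.

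| Share 11+ | n per arm, allowance needed | Power | n per arm, allowance spare | Power | Detectable d at 80% power, allowance needed |
|---|---|---|---|---|---|
| 62.5% | 26.2 | .60 | 30.4 | .66 | .63 |
| 70% | 29.4 | .65 | 34.0 | .71 | .60 |
| 73% | 30.5 | .67 | 35.3 | .73 | .585 |
| 80% | 33.6 | .71 | 38.9 | .77 | .56 |
| 90% | 37.8 | .76 | 43.7 | .82 | .53 |

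Detectable d = √(2 × VF / n) × 2.8016.

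**Step 5: share needed to keep .80.** 41.86/42 = 99.7% with the allowance needed; 41.86/48.6 = 86% with no dependency. If p is the fraction of children in the 8-12 group, evenly spread, the share aged 11 or older is 1 − .75p. A share of 86% then requires p = .14/.75, or about .19. Fewer than one child in five could be in the younger programme.

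**Step 6: recruitment that would keep 42 per arm aged 11 or older.** 162/.625 = 260, 162/.70 = 232, 162/.727 = 223 (rounded up), against 162 planned.

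**Sensitivity to the contrast.** With the mean of all four measurements (VF .625) the formula gives 40 per arm, not 42, and the range .60-.67 becomes .63-.70. Baseline-adjusted analysis of the three post-baseline means (VF = .667 − .25 = .417) needs 2 × .417 × 7.849/.25 = 26.2 per arm; power at 26.2 to 30.5 per arm would be .80 to .86. A single time point (VF = 1) needs 63 per arm, and power at 42 is already only .63.

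**The case against.** **The Sample size section makes no claim per instrument.** This is true. Psychosocial functioning is also measured by the CBCL and the SDQ parent form at all ages, so four of the six primary reports are unaffected. Table 2 also discloses the age limits openly. What remains is that all six are primary without ranking, one power figure is given, and nothing warns that it does not carry over to two of them. This is not detail left to an analysis plan: the primary status, the age limits and the sample size are all fixed in the article.

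**The size of the loss rests on an assumed age mix.** Also true. The direction does not: on the variance that reproduces 42, only a sample with very few children under 11 keeps .80.

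**A more efficient analysis could recover the loss.** Baseline adjustment could, as shown above. The article does not specify it, and the stated 42 does not rest on it. It would raise power for the all-age measures too (.94 at 42 per arm), so the gap between the two sets of measures would remain.

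**Stronger readings that the article does not support.** Three are tempting:
- *Children change primary instrument during follow-up.* None does. A child who turns 11 has no earlier form of the YSR or SDQ self-report to switch from; at most the child could start it without a baseline value. Paired age forms exist only for self-perception (CBSK at 8-12, CBSA at 12-18), a secondary outcome, and the article does not say that the form changes during follow-up.
- *A group × time model would read age-crossing as a treatment effect.* Allocation is randomised and scheduled separately by age group, so birthdays are expected equally in all arms. Crossing an age limit would add noise and missing baselines, not a systematic group × time effect.
- *Children pass an upper limit at 18.* This follows only if 18 itself is excluded, which the stated ranges do not say.

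**Conclusion.** The point holds in a narrow form. For the YSR and the SDQ child form, the stated .80 is not delivered on the plan's own inputs. With 62.5% to 73% of children aged 11 or older, about 26 to 31 per condition contribute and power is about .60 to .67, or .66 to .73 if the whole dependency allowance is spare.

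These figures assume a two-sided pairwise test, the variance factor that reproduces 42 per condition, and an age mix that the article does not give. The SDQ parent form, CBCL, QOK-c and QOK-p are not affected. The point is about reported power and the population to which conclusions apply; it shows no bias in the treatment comparison.

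**What to change.** In the Sample size section, state that .80 at d = .5 refers to the all-age primary measures: CBCL, SDQ parent form, QOK-c and QOK-p. For the YSR and the SDQ child form, give the expected number aged 11 or older and either the resulting power or the detectable effect (about d = .59 to .63 with 162 recruited, under the age mixes above), using the age distribution that the sponsor expects. State that these two forms are analysed in children aged 11 or older at baseline and that their conclusions are limited to that age range.

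The cost is a few sentences; recruitment, instruments and visits stay as they are.

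Making the two self-reports secondary is optional. QOK-c would keep a child-reported primary outcome, but psychosocial functioning would then rest on parent report alone. In the combined arm the reporting parent also receives the parent programme, so the rater's own treatment would be mixed with the outcome. Keeping the self-reports primary with their true power stated is a defensible choice.

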#### Parent-child interaction observation task

Six months after baseline assessment (T2) parent-child dyads are observed with a semi-structured parent-child interaction task. This task is an 30-minute observation paradigm in which parent and child collaborate on three different tasks: guiding marbles through a labyrinth, naming coping solutions for hypothetical situations using three different vignettes, and talking about personal disease related emotions and solutions. The three tasks differ in the level of collaboration and competition between parent and child. Observations of the interaction will be independently coded by trained graduate students, unaware of the child's treatment condition. In a study with 100 children (10-16 years old) with a wide range of psychological problems, this task has shown to be sufficient in identifying individual differences in parental responsiveness and granting autonomy support, child's positive affect and showing autonomy, and dyadic collaboration. Trained master students have shown to be reliable in administering and coding the observations (ICC = .74, range .66-.78) [34].

### Statistical analyses

The analyses will be performed on the basis of an intention-to-treat population. Treatment effects (group × time) will be assessed with linear mixed model analysis using SPSS. Intraclass correlations will be computed to test possible dependency effects of block randomization [35]. In secondary analyses, mediator variables will be included to investigate which underlying processes in children and families change as a result of the intervention. Moderator variables will be included to examine whether the effects are associated with characteristics of the child and the family (gender, age, medical diagnosis, severity of disease, attendance during group sessions).

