## Methods/design

### Interventions

#### Child intervention 'Op Koers'

'Op Koers' is based on techniques proven to be effective in behavioral and cognitive behavioral programs for children with somatic complaints [14] and in children with behavior and/or anxiety disorders [14]. 'Op Koers' has slightly different versions for two different age groups because of differences in cognitive development and age related topics. The first group consists of primary school children (8-12 years) and the second of adolescents in secondary school (12-18 years). The intervention takes place in the hospital were the child is medically treated, and involves six weekly 90 minutes sessions, and one return session after six months. To stimulate group processes and because of educational reasons groups with a minimum of four and a maximum of eight children are formed. The intervention aims to empower children with CI by teaching the active use of coping strategies. These coping strategies are translated into five learning goals: 1) information seeking and information giving about the disease ('good to know better' principle), 2) use of relaxation during stressful situations (using exercises), 3) increase knowledge of self-management and compliance, 4) enhancement of social competence (group discussions, role playing), and 5) positive thinking (effective use of the Thinking-Feeling-Doing model; replacement of inaccurate thoughts) [14]. During the group sessions the goals are translated into psycho-education (such as informative video's and group discussions), and reinforced and practiced through exercises (such as role-play and board games) and homework assignments. In all sessions age-appropriate examples are used.

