### Randomization

Participants are randomly allocated to the conditions within their own hospital. For each hospital, the assignment of participants is carried-out by using a block randomization method [17,18]. Interventions are organized at three time points (three cohorts), to spread recruitment over time. An allocation schedule is formulated in which the conditions (separately for each age group) will equally be divided across the centers and cohorts to ensure the number of groups is about the same within each condition. To ensure minimal differences between hospitals, participants will be considered in blocks of 12, 15, 18, 21 and 24 (4 to 8 in each condition), and in each centre heterogeneity of medical diagnosis is guaranteed. An independent researcher makes the allocation schedule using random allocation software.

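### Dependency is attributed to randomisation blocks, which span all three arms; the therapy groups, which can inflate the variance of the treatment contrasts, are not named

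*Protocol article*

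**What the plan says.** All points are from the protocol article.

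- **Statistical analyses.** Treatment effects (group by time) are assessed with a linear mixed model. On dependency the section says: "Intraclass correlations will be computed to test possible dependency effects of block randomization". It does not say what follows from a positive or a negative result.
- **Sample size.** Before inflation, "a sample size of 126, 42 in each condition, is necessary to achieve adequate power (.80"). The inflation is explained as follows: "To be able to control for dependency effects (block and centre effects) and taking into account 10% attrition over time, 162 children" are to be recruited. No ICC or cluster size is given.
- **Randomization.** Within each hospital, "participants will be considered in blocks of 12, 15, 18, 21 and 24 (4 to 8 in each condition").
- **Child intervention 'Op Koers'.** Treatment is delivered in groups: "groups with a minimum of four and a maximum of eight children are formed".
- **Parent intervention.** In one arm, parents also meet in groups, at the same time as their children's groups.
- **Study design.** The third arm is a one-year waiting list, so its children share no treatment group during follow-up.

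**The concern.** A block holds children from every condition. Whatever they share because of hospital, cohort or age group is present in all three arms, and it largely drops out when arms are compared.

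A therapy group is different. Its children share therapists, sessions and one another, and all of them are in the same arm. Its effect does not cancel and adds variance to the contrast. By the sizes given, a therapy group corresponds to one block-by-condition cell, not to a block. In the child-plus-parent arm, the parallel parent group adds a second shared influence.

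Both places where the article discusses dependency therefore name a unit that does little harm to the contrasts. Neither names the one that can. At stake is the error rate of the primary comparisons. The contrast between the two intervention arms is most exposed because both sides are clustered. It addresses a stated objective: whether the parent programme enhances the child programme.

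**Working it through.** **1. Reproducing the plan's figure.** Inputs (Sample size): "Based on four repeated measurements with within-subject correlations of .5", and "differences of medium effect size (d = .5) between the conditions over time at a significance level of .05", with power .80. Two-sided testing is assumed.

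- Variance factor for the mean of three post-baseline measures: V = (1 + 2 × .5)/3 = .667. Subtracting baseline gives the same: .667 + 1 − 2 × .5 = .667.
- n per arm = 2 × (1.960 + .842)² × .667/.5² = 41.9, so 42, or 126 in total. This matches.

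**2. The allowance within 162.** Attrition alone gives 126/.9 = 140. The 162 recruits leave 162 × .9 = 145.8 completers (48.6 per arm), so the implied design effect is 145.8/126 = 1.157.

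**3. What that supports.** Let m be the therapy-group size and D = 1 + (m − 1) × ICC. The variance of child-plus-parent versus child-only is multiplied by D. Against the unclustered wait-list the factor is (1 + D)/2. Setting each equal to 1.157:

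| m | ICC supported, between intervention arms | ICC supported, versus wait-list |
|---|---|---|
| 4 | .157/3 = .052 | .105 |
| 6 | .157/5 = .031 | .063 |
| 8 | .157/7 = .022 | .045 |

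**4. Error rate with no therapy-group term, and power once clustering is counted.** The ICC is assumed, m = 6, and there are 48.6 completers per arm. With f the variance factor, type I error = 2 × (1 − Φ(1.96/√f)) and power = Φ(.5/√(2 × .667 × f/48.6) − 1.96).

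| ICC | f, between intervention arms | Type I | Power | f, versus wait-list | Type I | Power |
|---|---|---|---|---|---|---|
| .02 | 1.10 | .062 | .82 | 1.05 | .056 | .84 |
| .05 | 1.25 | .080 | .77 | 1.125 | .065 | .81 |
| .10 | 1.50 | .110 | .69 | 1.25 | .080 | .77 |

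At ICC .05, type I error is .068 and .059 (between intervention arms; versus wait-list) for m = 4, and .092 and .071 for m = 8.

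**5. Would the stated check find it?** A block of 18 has 18 × 17/2 = 153 pairs of children. Of these, 2 × 15 = 30 share a therapy group, or 20%. A therapy-group ICC of .05 therefore appears as a block ICC of about .05 × .20 = .01.

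This was simulated with 9 blocks, 3 arms, 6 children per cell, a group effect in the two intervention arms only, and 20,000 runs:

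- A block-level test detected the clustering in 10% of trials at ICC .05 and 17.5% at ICC .10.
- At ICC .05, type I error (versus wait-list; between intervention arms) was .064 and .082 with no cluster term, and .066 and .084 with a block term. The block term corrected nothing.
- Analysis at therapy-group level held type I error at .048 to .052 across ICCs from 0 to .10.

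**6. Would a test at the right level be a safe guide?** With 54 recruits per arm and m = 6 there are 9 groups per arm. The F test on 16 and 90 degrees of freedom has power of 19% at ICC .05 and 41% at ICC .10. A negative result would say little.

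**The case against.** **The wording may be loose.** The 4 to 8 children per condition in a block match the therapy-group size, so block dependency may have been meant as the block-by-condition group. That is possible. But the Randomization section uses the word for sets spanning all conditions, and the Sample size section pairs block with centre. If therapy group was meant, the text still needs to say so.

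**The article is condensed.** It lists no random effects, and the full plan may include a therapy-group term. This stands: it is not shown that the group level is left out of the model. A reader might also fault the absence of terms for hospital, age group and cohort, but an article may leave those to the full plan. The point rests on the unit that the text does name.

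**No test-then-decide rule is written.** A reader might infer that a non-significant ICC leads to a model without clustering. The article does not say so, and its Sample size section speaks of controlling for dependency.

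**The sample was enlarged.** True, and it matters for power. Extra recruits do not correct standard errors from a model that omits the group level.

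**The error rates are upper values for a given ICC.** They assume no shared block or centre variance. If such variance exists and is unmodelled, it widens standard errors and offsets part of the problem. With an assumed shared block ICC of .05, group ICC of .05 and m = 6, the factors become 1.20 and 1.075 and type I error about .074 and .059. Counting 145.8/27 = 5.4 completers per group in place of 6 gives .076 and .063 without block variance. Both reduce the size somewhat; neither removes it.

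**Conclusion.** The concern holds as a wrong unit stated in the text. Block and centre effects largely cancel from the contrasts. Therapy-group effects do not, and a block-level ICC or block term would largely miss them.

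The consequence is conditional. Standard errors are too small if the therapy-group ICC exceeds 0 and no therapy-group term is fitted. A reader might conclude that they certainly will be, but the article gives neither the ICC nor the random effects. Under the assumed range the effect is modest against wait-list and larger between the two intervention arms.

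It would also go too far to say that 162 covers only a very small ICC. At 6 per group, the limit of about .03 applies to the contrast between the intervention arms. Against wait-list, the comparison for which the Discussion calls the sample sufficient, it is about .06. The figures rest on equal group sizes and a normal approximation, with the ICC taken on the scale of the analysed outcome.

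**What to change.** **Statistical analyses.** Name the therapy group (the block-by-condition cell) as the clustering unit. In every primary model, fit it as a random effect in the two intervention arms only, with wait-list children as singletons (a partially nested model). Do this whatever the ICC test shows; the estimated ICC can still be reported.

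**Sample size.** State that the rise from 140 to 162 is a design effect of 1.157. At 6 per group it supports a therapy-group ICC of about .03 between the two intervention arms and about .06 versus wait-list. Give power for both contrasts at ICC .05 and .10: .77 and .69 between the intervention arms, .81 and .77 versus wait-list.

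**Cost.** A few lines of model specification, which the mixed-model procedure in SPSS can fit, and a record of each child's group. Intervals become slightly wider and the stated power slightly less favourable.
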